## Methods and analysis

### Trial design and registration

This is a parallel, two group, randomised controlled, statistician-blinded efficacy trial to evaluate whether AI spirometry decision support software can improve the performance of primary care clinicians in their interpretation of real-world spirometry. Each clinician will be provided with the same clinical dataset of 50 de-identified, real-world patient spirometry records through an online platform (Qualtrics XM), and asked to answer questions about preferred diagnosis (ie, diagnosis they think is most likely) and differential diagnosis (ie, second most likely diagnosis) based on spirometry and limited clinical data, the technical quality of spirometry and the spirometry pattern. Questions will also explore clinicians’ confidence in their assessments.

Participants will be allocated at random to receive either spirometry records alone or spirometry records with the addition of the AI software report. The clinical spirometry records will be de-identified (name, date of birth, address, postcode, occupation, GP, medications data removed), by a member of the clinical care team.

Royal Brompton and Harefield Hospitals (RBHH), Guy’s and St Thomas’ NHS Foundation Trust (GSTFT) will act as study sponsor. This study has been reviewed and given favourable opinion by Health Research Authority (HRA) Wales (reference: 22/HRA/5023).

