### Procedure

Study participants (participating clinicians) will independently assess the same 50 spirometry records, in the same order, through a bespoke designed online platform developed using Qualtrics XM (Seattle, USA). Participants will be blinded to the reference standards. See figure 1 for example. The patient spirometry records were randomly selected from a database comprising 1122 patients undergoing spirometry in primary care and community-based respiratory clinics in Hillingdon borough between 2015 and 2019. An online randomiser will be used to select the 50 spirometry sessions used in the trial (https://www.randomizer.org/), according to ‘disease category’ so that of the 50 spirometry traces selected, 40% will be from patients with COPD, 20% will have normal spirometry and 10% for each of the four other disease categories (asthma, interstitial lung disease (ILD), other obstructive, other disease/unidentifiable category), to represent a likely distribution of diagnoses in a primary care setting.

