### Sample size calculation

The sample size calculation was informed by previous feasibility data from 30 primary care practitioners assessing five spirometry traces. The preferred diagnosis matched the reference diagnosis in a mean (SD) of 55% (19%) of spirometry records. We have assumed the same SD of 19%, which is conservative because more cases will be assessed per practitioner, leading to less variable practitioner rates. As the calculation involves conservative assumptions, the power was set below 90%, to be 85%. With 132 participants (66 per group) this allows for detection of a 10% difference (a mean of 5 extra cases in 50) in the rate of cases correctly identified to match the reference standard (mean 65% vs mean 55%) using an unpaired t-test at the two-sided 5% significance level.

The recruitment target was originally estimated at 156 practitioners to allow for an estimated 15% drop out. However, a preliminary analysis of completion rate of the first 50 recruited participants demonstrated that 29 of the 50 participants scored all 50 spirometry records within the 8-week study period (58% completion). Based on this data, the study statistician advised increasing the recruitment target to 228 to account for 42% non-completion (see the Amendment section).

Descriptive statistics will be performed for demographics, baseline characteristics and endpoint data: number and percentage for categorical data and mean and SD or median and interquartile range (IQR) for non-normally distributed continuous data.

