#### Primary endpoint analysis

For each participant, diagnostic performance will be calculated as percentage of the 50 spirometry procedures where the final diagnosis was correctly identified. In each randomised group, the diagnostic performance will be summarised as the mean of the participants’ diagnostic performance. A two-sample unpaired t-test will be used to assess the mean difference in correct response between the two randomised groups. The assumptions for the two-sample t-test will be tested and where the assumption for equal variances fails then the Welch t-test will be used.

Randomisation will be stratified according to job role (GP: yes or no) and Accreditation from Association for Respiratory Technology and Physiology (performance only, interpretation only, performance and interpretation, no accreditation), therefore an analysis of covariance will be used to compare the intervention and control groups by adjusting for the main effects of the stratified variables. To internally validate the estimate of the difference between the two groups bootstrap estimation of difference will be done by taking 100 from the analysis of covariance model or Welch's t-test.

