## Discussion

Spirometry is a key investigation for supporting diagnosis and disease monitoring in chronic respiratory disease. There is a clear need to improve the access, quality and interpretation of spirometry in primary care and other non-respiratory community settings which have many historic challenges, further negatively impacted by the COVID-19 pandemic.^8^ AI decision-support software has shown potential in improving quality assessment and interpretation of spirometry and this study will evaluate its effectiveness in interpretation of real-world spirometry results assessed by clinicians working in primary care in the UK.

This study is the first randomised controlled efficacy study with an intervention designed to improve the performance of primary care clinicians in the interpretation of spirometry using AI and an important first step for clinicians to make informed choices about its use. It will directly test the effect of an AI-powered spirometry interpretation software in primary care using real-world traces reflective of the results reviewed in practice by clinicians.

We will advertise the trial and recruit nationally to maximise participation and variation in participant sample.

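### The planned interval is valid for these 50 traces but omits variation between traces in the AI effect, so it is too narrow for claims about primary care spirometry

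*Protocol article*

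**What the plan says.** Under Trial design and registration: "Each clinician will be provided with the same clinical dataset of 50 de-identified, real-world patient spirometry records". The Eligibility criteria section adds that the intervention arm also receives an AI report for each record. Under Procedure, the traces are a sample: "The patient spirometry records were randomly selected from a database comprising 1122 patients". Selection followed fixed disease quotas (40% COPD, 20% normal, 10% for each of four other categories), meant to mirror the mix seen in primary care. The source is one borough, 2015 to 2019.

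The Primary endpoint analysis section forms one percentage per clinician. It then states: "A two-sample unpaired t-test will be used to assess the mean difference in correct response between the two randomised groups". Welch's test is used if variances differ, followed by an ANCOVA on job role and accreditation. A bootstrap is tied to the same estimate. No trace term and no resampling of traces is described. Secondary endpoint analysis carries the approach over.

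Two targets appear. The Introduction words the primary objective as performance on the 50 records. The Abstract and the trial design section speak of spirometry interpretation generally, and the Discussion says: "It will directly test the effect of an AI-powered spirometry interpretation software in primary care using real-world traces".

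**The concern.** The design crosses clinicians with traces. Because the AI output for a trace is common to the whole intervention arm, any excess or shortage of correct AI reports among the 50 drawn traces moves all intervention scores together. A standard error built from differences between clinicians cannot see that shared error. Recruiting more clinicians does not reduce it; only more traces would.

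What is omitted is specific. Both arms read the same traces, so trace difficulty largely cancels from the difference. What remains is the arm-by-trace component: the AI helps on some traces and misleads on others. If the interval is then read as evidence about the software in primary care, it overstates certainty.

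**Working it through.** **The plan's own figure.** Inputs from the Sample size calculation section: SD 19 points, difference 10 points, 66 per group, power 85%, "using an unpaired t-test at the two-sided 5% significance level". The noncentral t distribution gives 84.6% power at 65 per group and 85.1% at 66, so 132 is right. Then 132/0.85 = 155.3, rounded up to 156, and 132/0.58 = 227.6, rounded up to 228. The arithmetic is correct for random clinicians and fixed traces.

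**Adding the trace component.** Let τ be the SD across traces, within disease category, of the AI effect on the percentage correct. The protocol gives no τ, so 5 to 30 points is an assumption.

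- Clinician part: SE_c = SD × √(2/66). SD 19 gives 3.31; SD 10 gives 1.74.
- Trace part: SE_t = τ/√50, which is 0.71, 1.41, 2.83 and 4.24 for τ = 5, 10, 20 and 30.
- Total: SE = √(SE_c² + SE_t²).
- Coverage of the planned interval for the trace population: 2Φ(1.96 × SE_c/SE) − 1.

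Example, SD 19 and τ 20: SE = √(3.31² + 2.83²) = 4.35, and 1.96 × 3.31/4.35 = 1.49, so coverage is 86.4%.

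Half-widths and power below use the total SE with Satterthwaite degrees of freedom; power is for a true 10-point effect.

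| τ | Coverage, SD 19 | Half-width, SD 19 | Power, SD 19 | Coverage, SD 10 | Half-width, SD 10 | Power, SD 10 |
|---|---|---|---|---|---|---|
| 0 | 95% | 6.5 | 85% | 95% | 3.4 | >99% |
| 5 | 94.5% | 6.7 | 84% | 93% | 3.7 | >99% |
| 10 | 92.8% | 7.1 | 79% | 87% | 4.4 | 99% |
| 20 | 86.4% | 8.6 | 63% | 70% | 6.6 | 85% |
| 30 | 77.2% | 10.7 | 45% | 54% | 9.2 | 58% |

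**Why SD 10 is shown.** The plan says: "We have assumed the same SD of 19%, which is conservative because more cases will be assessed per practitioner". The 19 comes from five traces per practitioner. Binomial noise alone at 55% is √(0.55 × 0.45/5) = 22 points with five traces and √(0.55 × 0.45/50) = 7 points with 50. A realised SD well below 19 is therefore likely. The value 10 is an assumption.

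**What τ might be (assumed cases, ignoring the quotas).** If the AI is right on 70% of traces and shifts accuracy by +25 points when right and −25 when wrong, the mean effect is 0.7 × 25 − 0.3 × 25 = 10. Then τ = 50 × √(0.7 × 0.3) = 22.9, and SE_t = 3.2, about the whole planned SE of 3.31. If it is right on 80% and shifts +15 or −10, the mean is again 10, but τ = 25 × √(0.8 × 0.2) = 10 and SE_t = 1.41.

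**Simulation check.** Crossed clinician-by-trace data, 66 per arm, 50 traces, clinician-score SD about 10, 4,000 runs per setting. For τ = 0, 5, 10, 20 and 30 the planned interval covers the effect on the drawn 50 traces 95, 96, 95, 95 and 95% of the time, and the trace-population effect 95, 93, 89, 73 and 59%. The second series is slightly above the formula at the larger τ because probabilities were truncated at 0 and 1, which shrinks the effective τ.

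**Dependence on reliance.** In a second simulation (clinicians 55% correct, AI assumed 65% correct, implied clinician SD about 8), coverage was about 77% when the AI was followed on 30% of cases and 57% at 50%. At 10% following it was 93 to 94%.

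**COPD subgroup.** With 20 traces the trace part is τ/√20, which is √(50/20) = 1.6 times larger.

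**The case against.** The strongest reply is that nothing is wrong for the stated objective. The Introduction names the 50 records, the endpoint is a percentage of those records, and clinicians are the randomised unit. That stands in full. A reader might infer a unit-of-analysis error or an invalid primary test; coverage of about 95% for the effect on these traces, at every τ, shows otherwise. A rejection that arises because the AI happened to do well on the drawn traces is also correct for those traces.

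A reader might infer that the trial is underpowered. The documents do not support that as a finding: 132, 156 and 228 all reproduce, and the loss of power in the table turns on an assumed τ. With SD 10 and τ 20, power is still 85%.

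The size is indeed not known. The protocol gives no AI accuracy, follow rate or τ, so no single coverage figure may be quoted as fact. The quotas also remove between-category variation from the trace error, which is why τ is defined within category.

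Finally, Secondary endpoint analysis promises the AI's own accuracy against the reference, which shows readers how often it was right on these traces, and a crossed analysis may sit in the analysis plan, which is not at hand. Neither changes what the protocol fixes: a test, covariates and bootstrap without a trace term, alongside a claim that reaches past the 50 traces.

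**Conclusion.** The planned comparison is sound for these 50 records. Its interval is too narrow for the effect of the software on primary care spirometry whenever the AI effect varies between traces; the direction is certain for any τ above zero, the size is not. Over the assumed range, true coverage of a nominal 95% interval runs from 94.5% down to 77% with SD 19, and from 93% down to 54% with SD 10. It is close to nominal if clinicians rarely follow the AI. Treating the 1122 records as a finite population hardly helps: √(1 − 50/1122) = 0.98, about a 2% reduction in the trace part. This concerns the interval and the scope of the conclusion, not the sample size. It should be changed because the change is cheap.

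**What to change.** Keep the ANCOVA as the primary analysis and state that its interval is conditional on these 50 traces.

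Pre-specify one supportive analysis:

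- a mixed model of correct/incorrect with crossed random effects for clinician and trace and a random arm-by-trace effect, with disease category and arm-by-category as fixed effects to respect the quotas; or
- a bootstrap that resamples clinicians and, within disease category, traces.

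Report the marginal difference in percentage correct with its interval. Use that interval for any claim beyond the 50 traces, limited to the sampled population (one borough, 2015 to 2019); it would not by itself support a claim about UK primary care. Do the same for the 20-trace COPD subgroup.

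The cost is some wording, a little more analysis and a wider, less favourable interval. Responses are already recorded case by case, so no new data are needed.

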### Statistical analysis

Survey responses from participants will be collated in a secured, online database. A Statistical Analysis Plan will be developed and statistical analysis will be conducted by the study statistician. The statistician will be blinded to control/intervention group allocation. Descriptive statistics will be presented for demographic, baseline characteristics and endpoint data. Number and percentage will be presented for categorical data. Mean and SD will be presented for normally distributed continuous data while median IQR will be presented for non-normally distributed continuous data.

The number of participants consented, randomised, and completing the study will be described in a study Consolidated Standards of Reporting Trials diagram.

Data analysis will be performed on an intention to treat basis. Data will be analysed with the statistical software Stata V.17.0. All statistical tests will be two-sided and significance set at p<0.05.

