#### Secondary endpoint analysis

For continuous variables, the secondary endpoints will be compared between the control and intervention groups using the same approach as the primary endpoint.

The diagnostic prediction performance of the AI software alone compared with the reference diagnosis by the pulmonologists will also be reported.

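### The unequal-variance rule covers only the unadjusted t-test; the ANCOVA has none, so its standard error can be off if both spread and analysed numbers differ between arms (minor)

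*Protocol article*

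**What the plan says.** The section Primary endpoint analysis sets out two comparisons of the same percentage score. The first is a two-sample t-test whose assumptions will be checked: "where the assumption for equal variances fails then the Welch t-test will be used". The second follows from the randomisation by job role and accreditation: "an analysis of covariance will be used to compare the intervention and control groups by adjusting for the main effects of the stratified variables". No variance estimator is named for the second. The section ends with a bootstrap of the group difference, with 100 taken from the ANCOVA model or from Welch's test, as an internal validation of the estimate.

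Secondary endpoint analysis treats continuous endpoints "using the same approach as the primary endpoint". Statistical analysis fixes the level: "All statistical tests will be two-sided and significance set at p<0.05".

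Two other sections bear on how many participants each arm contributes. Sample size calculation reports that "29 of the 50 participants scored all 50 spirometry records within the 8-week study period (58% completion", which raised the recruitment target to 228. Missing data limits the primary analysis to participants who complete at least 70% of the cases.

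**The concern.** The article anticipates unequal variances and acts on them in one of its two analyses. If the variance check fails, Welch's test drops the adjustment for the randomisation factors, while an ordinary ANCOVA keeps the assumption that has just been rejected. No model-based analysis in the section both adjusts and tolerates unequal variances.

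The conditions that make this matter are plausible here. Every intervention participant sees the same AI report for a given record. That could draw scores together, or spread them out if some follow the report and others do not. Analysed numbers depend on who completes enough of the cases as well as on the 1:1 allocation, and the intervention changes the task being completed. If the less variable arm also keeps more participants, the ANCOVA standard error is too small and false positives exceed 5%. In the opposite case the interval is too wide and power is lost.

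**Working it through.** **The plan's own figures.** Inputs from Sample size calculation: difference 10 points, SD 19, power 85%, two-sided 5%. The noncentral t distribution gives power of 84.6% at 65 per arm and 85.1% at 66, so 66 per arm (132 in all) is right. Inflation: 132/0.85 = 155.3, so 156; 132/0.58 = 227.6, so 228. All reproduce, and the point below does not touch them.

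**Assumed inputs.** The documents give one SD (19, taken as common to both arms) and one overall completion rate. SDs and analysed numbers by arm are therefore assumptions: 132 analysed, control SD 19, intervention SD from 19 down to 9.5, and splits from 66/66 to 52/80 and 80/52.

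**Size of the error in the standard error.** With arm sizes n1, n2 and SDs s1, s2:

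- pooled variance = [(n1−1)s1² + (n2−1)s2²]/(n1+n2−2)
- pooled SE = √[pooled variance × (1/n1 + 1/n2)]
- true SE = √(s1²/n1 + s2²/n2)

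Control 56, intervention 76, SD 19 v 12: pooled variance = (55×361 + 75×144)/130 = 235.8; pooled SE = √(235.8 × 0.03102) = 2.70; true SE = √(6.446 + 1.895) = 2.89; ratio 0.94.

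Control 76, intervention 56, same SDs: pooled variance 269.2; pooled SE 2.89; true SE 2.71; ratio 1.07.

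In large samples the squared ratio is about (n1s1² + n2s2²)/(n2s1² + n1s2²). It equals 1 when n1 = n2, whatever the SDs, and it depends on the split and the SD ratio rather than on the total. A larger trial with the same split would not cure it.

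**Type I error.** Null trials were simulated (8,000 per row, Monte Carlo error about 0.25 points) with an ANCOVA on arm, GP status and four-level accreditation. The covariate mix and covariate effects were assumed.

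| Analysed, control/intervention | SD, control/intervention | Pooled SE ÷ true SE | Type I error, one variance | Type I error, HC3 |
|---|---|---|---|---|
| 66/66 | 19/19 | 1.00 | 4.5% | 4.1% |
| 66/66 | 19/12 | 1.00 | 4.7% | 4.2% |
| 66/66 | 19/9.5 | 1.00 | 5.6% | 5.1% |
| 62/70 | 19/12 | 0.97 | 5.8% | 4.8% |
| 70/62 | 19/12 | 1.03 | 4.1% | 4.2% |
| 60/72 | 19/15 | 0.98 | 4.9% | 4.0% |
| 56/76 | 19/15 | 0.97 | 5.8% | 4.8% |
| 76/56 | 19/15 | 1.04 | 4.2% | 4.4% |
| 56/76 | 19/12 | 0.94 | 6.7% | 4.6% |
| 76/56 | 19/12 | 1.07 | 4.0% | 4.7% |
| 56/76 | 19/9.5 | 0.91 | 7.5% | 4.7% |
| 76/56 | 19/9.5 | 1.10 | 3.3% | 4.6% |
| 52/80 | 19/12 | 0.91 | 6.8% | 4.3% |
| 80/52 | 19/12 | 1.10 | 3.3% | 4.6% |

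An extreme case, 52/80 with SD 12 v 6, has pooled SE 1.58 against a true 1.79 (ratio 0.88) and a type I error of about 8.2%.

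**How likely is such a split?** With 114 randomised per arm and the same 58% retention in each, the difference in analysed numbers has SD √(2×114×0.58×0.42) = 7.5. A gap of 20 (56/76) is 2.7 SDs, so chance alone will rarely produce it. It corresponds to retention of 56/114 = 49% against 76/114 = 67%.

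**The case against.** Several points on the other side carry weight.

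- **The detail may sit in the analysis plan.** The article never says that the ANCOVA will pool variances. That is inferred from the method's default, and an SAP is announced but not shown. This stands as a limit on the claim. It does not remove the point, because the article itself states an unequal-variance rule and attaches it to only one of two analyses of the same endpoint.
- **The bootstrap may help.** If whole participants are resampled, its standard error needs no common variance. In simulations with 100 replicates and a normal-based interval, the bootstrapped ANCOVA rejected 5.4% (75/57 analysed, SD 6 v 12) and 5.5% (80/52, same SDs), against 6.8% and 7.8% for the ordinary ANCOVA. But the resampling scheme is not stated and the stated purpose is validation, so it mitigates the gap without clearly closing it.
- **The powered test is protected.** The sample size rests on the unpaired t-test, which has the Welch fallback. True, though the adjusted comparison is also planned.
- **The adverse cases are assumed.** The 58% refers to completing all 50 records. The analysed set needs only 70% of them, so retention into the analysis can only be the same or higher. An SD of 6 lies below the simple binomial SD for 50 cases at 65% correct, √(0.65×0.35/50) = 6.7 points, so the 12 v 6 case is an extreme.

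A reader might go further and infer that the adjusted result is wrong whenever spread and numbers differ, or that unequal spread is built into the design. The documents support neither. Mild differences barely move the error rate. No SDs by arm are given, and a shared AI report could either narrow or widen the spread.

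**Conclusion.** The inconsistency is real and minor. The ANCOVA lacks the unequal-variance provision that the t-test has, and by default it assumes one residual variance. With similar retention the standard error is off by about 3% at most and type I error stays within about 1 point of 5%. A material effect, roughly 6% to 8% or 3% to 4%, needs two things together: a split near 56/76 or wider, which in practice means different retention by arm, and an SD ratio of about 1.5 or more. Both are plausible with 42% non-completion and a shared AI report, but neither is documented. The estimated difference is unbiased and the sample size is unaffected. The error rates rest on the assumed SDs, splits and covariate mix, and on normal errors.

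**What to change.** State that the ANCOVA will use heteroscedasticity-robust (HC3) standard errors from the outset, for the primary endpoint and for the continuous secondary endpoints, with no preliminary variance test. In Stata: `regress score i.arm i.gp i.accreditation, vce(hc3)`. HC3 cannot be computed when an accreditation level holds a single analysed participant, so say beforehand, blind to arm, how such a level will be merged with a neighbouring one. If the bootstrap is kept, state what is resampled.

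The cost is one option in the code and one or two sentences in the analysis plan, best added before allocation is unblinded. With equal variances and equal arms the interval is about 2% wider. Across the tabulated scenarios HC3 kept type I error between 4.0% and 5.1%.

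### The bootstrap check on the primary comparison is set at 100, too few for a reliable check, and does not say which of two models is resampled (minor)

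*Protocol article*

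**What the plan says.** The protocol article, under Primary endpoint analysis, sets out three steps. First, "A two-sample unpaired t-test will be used to assess the mean difference in correct response between the two randomised groups", with the proviso that "where the assumption for equal variances fails then the Welch t-test will be used". Second, because of the factors used at randomisation, "an analysis of covariance will be used to compare the intervention and control groups by adjusting for the main effects of the stratified variables". Third comes a bootstrap, whose purpose is given as "To internally validate the estimate of the difference between the two groups" and whose method is that "bootstrap estimation of difference will be done by taking 100 from the analysis of covariance model", with Welch's t-test given as the alternative source.

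Two things about the third step are visible in the text. The count is fixed at 100, but the thing counted is not named. Two source analyses are joined by an 'or', with no selection rule. The section names no bootstrap output: no percentile interval, no bootstrap standard error and no rule for what would count as agreement.

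**The concern.** A validation step should be more stable than the doubt it is meant to settle. With 100 resamples, a 95% percentile limit rests on the two or three most extreme values in each tail, so the answer moves noticeably with the random seed. If the trial result were close to the significance boundary, the check could disagree with the main analysis for no reason other than chance in the resampling.

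The open choice of model adds to this. Welch's test is planned only if equal variances fail. The ordinary t-test, which is the default unadjusted analysis, does not appear in the bootstrap sentence at all. If variances look equal, the sentence either means the analysis of covariance or names a test that would not have been run. The target of the check could then be chosen after the results are known.

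**Working it through.** **Inputs.** From Sample size calculation: SD 19 percentage points, 66 per group, a 10-point difference (65% against 55%), 85% power, two-sided 5%. From Primary endpoint analysis: B = 100, read as resamples.

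**The plan's own figure.** With SD 19 and a 10-point difference, the noncentral t distribution gives power of 84.6% at 65 per group and 85.1% at 66. The stated 66 per group is reproduced, so these inputs are a fair basis.

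**Standard error of the difference.** 19 × √(2/66) = 3.31 points. The 95% interval is about 2 × 1.96 × 3.31 = 13.0 points wide. The planned effect is 10/3.31 = 3.02 standard errors.

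**Simulation error by number of resamples.** Three formulas apply:
- bootstrap mean: SE/√B
- bootstrap SE, relative error: 1/√(2(B − 1))
- one 95% percentile limit: √(0.025 × 0.975/B)/φ(1.96), in units of SE

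| B | Mean (points) | Relative error of SE | One limit (SE) | One limit (points) |
|---|---|---|---|---|
| 100 | 0.33 | 7.1% | 0.267 | 0.88 |
| 2000 | 0.07 | 1.6% | 0.060 | 0.20 |
| 5000 | 0.05 | 1.0% | 0.038 | 0.12 |

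Simulation of the limit at B = 100 gives about 0.24 SE, or 0.8 points, so 0.8 to 0.9 points is a fair range.

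**Coverage of a 95% percentile interval.** At B = 100, simulated coverage is 92.4% (3000 simulated trials with 66 per group) and 93.2% (normal approximation). At B = 2000 it is 94.8%.

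**Borderline result.** Take z = 2.2 (p = 0.028), a difference of 2.2 × 3.31 = 7.3 points. Each resample falls below zero with probability Φ(−2.2) = 0.0139, so 1.39 of 100 are expected to do so. The interval includes zero if enough resamples fall below zero:
- limit taken as the 3rd smallest value: P(3 or more of 100) = 16%
- limit taken as the 4th smallest value: P(4 or more of 100) = 5%
- interpolated percentile, by simulation: 9 to 10%
- B = 2000, limit at the 50th smallest: about 0.0001
- B = 5000, limit at the 125th smallest: about 10⁻⁹

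**Planned effect.** At z = 3.02 each resample falls below zero with probability 0.00125. Even the 3rd-smallest rule then includes zero with probability of only 0.0003. On one fixed data set with a 10-point difference, the lower limit at B = 100 ran from 2.2 to 5.3 points across 95% of reruns, and was below zero in none of 4000.

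**Share of total uncertainty.** Simulation variance relative to sampling variance is 0.24² to 0.27², or about 6 to 7%. As a share of a limit's total variance it is about 5 to 7%.

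**The case against.** The strongest reply is that the bootstrap is supplementary. Significance is judged by the t-test or Welch test and by the analysis of covariance, and none of these uses it. The section speaks of validating the estimate of the difference and names no interval. For the mean of the resampled differences, 100 resamples give an error of 0.33 points against a 10-point target, which is rough but usable. The 'or' can be read as bootstrapping whichever analysis is used. Details such as the seed, the interval type and the resampling scheme normally sit in a statistical analysis plan, which the article says will be developed and which is not shown.

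Most of this stands, and it limits the point to a minor one. It does not remove it, because the count of 100 and the unresolved 'or' are written into the article itself.

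A reader might also infer more than the document supports:
- **That simulation noise dominates the limits.** Sampling error is about four times larger, as the variance share shows.
- **That the bootstrap cannot validate the result, or that a new seed could reverse the trial's conclusion.** Only a borderline result could be contradicted, only if percentile limits are reported, and the main tests would be unaffected.
- **That the check fails because it does not resample the spirometry records.** The stated objective concerns the same 50 records for every clinician. Whether to generalise to other records is a separate question about the estimand, on which statisticians may differ. A clinician-level bootstrap still serves to check normal-theory inference for bounded percentage scores.

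**Conclusion.** The point holds at low severity. As written, the check is less precise than it needs to be, and its target model is not settled. The 7% relative error in the bootstrap standard error depends only on B = 100. The limit error in points, the coverage shortfall and the roughly 10% contradiction rate at z = 2.2 further assume that percentile limits are reported. The figures in points also use the planning SD of 19 and 66 analysed per group. With an assumed SD of 10 the limit error would fall to about 0.47 points, but its share of the standard error would be the same. All of this reads the missing noun as resamples.

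**What to change.** In Primary endpoint analysis:
- State that the number counts bootstrap resamples.
- Raise it to at least 2000. With 5000, the error of a percentile limit falls to about 0.12 points.
- Replace the 'or' by the one model that is named as the primary analysis.

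The cost is one number and one phrase, plus minutes of computing in Stata, which the protocol already specifies. No data collection, sample size or main test changes.
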